### Sample size calculation

The sample size calculation for this study was based on data obtained from a pre-trial conducted between October 2024 and January 2025. In the pre-trial, 24 post-stroke tracheostomy patients meeting the study’s inclusion and exclusion criteria were enrolled and randomly assigned to either the TFRL-IMT group (*n* = 12) or the conventional treatment group (*n* = 12). In the conventional treatment group, 6 patients were successfully extubated, resulting in a 50% decannulation success rate. In the TFRL-IMT group, 10 patients were extubated, with an decannulation success rate of 83.3%. The between-group difference in decannulation success rates was 33.3%. Based on the preliminary results and relevant literature (5), the decannulation success rate was conservatively estimated to be 50% in the control group and 80% in the TFRL-IMT group, yielding an expected effect size of 30%.

The sample size was calculated using PASS 15.0 software (NCSS, LLC, Kaysville, UT, United States). A significance level of *α* = 0.05 (two-sided) and statistical power (1 − *β*) = 80% were adopted based on literature recommendations (27). Assuming an decannulation success rate of 50% in the control group and 80% in the TFRL-IMT group, the required sample size for each group was calculated to be 26. Based on the preclinical follow-up experience of the research team, an expected attrition rate of 15% was applied. According to the adjustment formula *n*’ = *n*/(1 − f), where *n* is the unadjusted sample size and f is the expected attrition rate (28), the adjusted sample size per group was calculated as *n*’ = 26/(1–0.15) ≈ 30. Therefore, the finalised total sample size was determined to be 60.

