### Intervention protocol

#### Experimental group interventions

In this study, patients in the experimental group will receive TFRL-IMT in addition to conventional treatment. TFRL-IMT will be administered using the inspiratory muscle training module of a portable pulmonary function testing device (X1, Seck Medical Devices Co., Ltd., Xiamen, China). The initial training load will be set at 30% of the subject’s MIP, which will be measured using the device’s built-in function. During the study period, MIP will be measured weekly, and the training load will be adjusted to 30% of the current MIP. Additionally, resistance will be gradually increased by 5% per week until 60% of MIP is reached and maintained, depending on the patient’s tolerance.

The training programme will last for 3 weeks, during which patients will undergo two sessions per day, each comprising five sets of six maximal inspiratory efforts with a one-minute rest between sets. During each session, the patient’s tracheal cannula will be connected to the device valve via a specialized connecting tube, and the patient will be instructed to inhale as forcefully and rapidly as possible, followed by slow exhalation. All training will be conducted under the supervision of healthcare professionals to ensure training quality and patient safety. The rehabilitation therapist will document the actual load, completion status, and any adverse events during each training session.

In patients with concurrent respiratory infections, appropriate antibiotics will be administered based on clinical manifestations and sputum culture results. In patients with thick sputum, nebulized salbutamol (2.5 mg) combined with ipratropium bromide (0.5 mg) will be administered three times daily at 8:00 a.m., 12:00 p.m., and 8:00 p.m.

To evaluate the efficacy and safety of the intervention, MIP values will be measured before and after training using the same portable pulmonary function device. Simultaneously, vital signs such as including heart rate, blood pressure, respiratory rate, and oxygen saturation will be continuously monitored.

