#### Primary outcome

The primary outcome will be the decannulation success rate following the 3-week intervention. Successful decannulation will be defined as the absence of reintubation within 72 h following tracheostomy tube removal. The decannulation process will adhere to a strictly standardised protocol, with specific criteria as follows: minimal secretions with effective clearance; good cough function (peak cough flow >160 L/min); absence of hypoxaemia (SpO2 ≥ 92%), respiratory distress, or reduced level of consciousness during a 24 h continuous tracheostomy tube occlusion test; and normal swallowing function. The decannulation success rate will be calculated as the proportion of successful decannulation relative to the total number of cases treated and expressed as a percentage. This outcome will be assessed at the end of the 3-week intervention.

Decannulation failure will be defined as the occurrence of any of the following conditions within 72 h post-decannulation: severe respiratory distress (respiratory rate >35 breaths/min); persistent hypoxaemia (requiring FiO2 > 0.5 to maintain SpO2 ≥ 90%); hypercapnia (PaCO2 > 50 mmHg and pH < 7.30); or clinical need for reintubation.

To ensure objectivity and accuracy, decannulation decisions will be made jointly by at least two therapists and rehabilitation physicians who are blinded to patient group allocation. This double-blind assessment design minimizes bias and enhances the reliability of study outcomes.

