#### Secondary outcomes

Secondary outcomes will include diaphragmatic function, respiratory parameters, clinical outcomes, and quality of life.

Diaphragm function will be evaluated using a portable ultrasound device (SII, Sonosound Medical Devices Co., Ltd.). Diaphragm excursion will be measured using M-mode ultrasound. Patients will be positioned semi-recumbently, and a trained sonographer will use a convex-array probe placed at the mid-axillary line beneath the right costal margin to obtain the maximal diaphragm excursion during quiet breathing. Each measurement will be repeated three times and averaged. Diaphragm thickness will be measured with B-mode ultrasound using a high-frequency linear-array probe placed along the anterior axillary line at the 8th to 9th intercostal space, the thickness will be assessed at end-expiration and end-inspiration. All measurements will be performed at baseline (pre-intervention) and after 3 weeks of intervention.

Respiratory parameters, including MIP, forced vital capacity (FVC), peak expiratory flow (PEF), and forced expiratory volume in one second (FEV1), will be assessed using a portable spirometer (X1, Seck Medical Devices Co., Ltd., Xiamen, China). The tracheostomy cuff is inflated to 25 cmH₂O with patients in a semi-recumbent position (45°). For MIP assessment, patients will perform five maximal inspiratory efforts from end-expiratory volume, with the highest value being recorded from three reproducible trials, each demonstrating <10% variation. For spirometric parameters (FVC/PEF/FEV1), patients will perform three forced expiratory maneuvers from total lung capacity with ≥30 s rests between trials, adhering to ATS/ERS standards. Specifically, FVC will use the highest value from ≥2 reproducible trials (<5% variation), PEF will take the highest peak flow from any valid trial, and FEV1 will use the highest value from ≥2 trials with acceptable start-of-test criteria. All measurements will be performed at baseline (pre-intervention) and after 3 weeks of intervention.

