Clinical outcome indicators will include the length of hospital stay, the incidence of respiratory-related complications, and the rate of reintubation within 72 h following decannulation. Relevant data will be extracted from patients’ electronic medical records. Length of stay will be defined as the total number of days from study enrollment to hospital discharge. Respiratory-related complications will be defined to include common conditions such as pneumonia, atelectasis, and pneumothorax. All clinical outcome indicators will be recorded by a designated study physician.

Quality of life will be evaluated using three instruments: the EQ-5D-5L Health-Related Quality of Life Questionnaire, the Breathing Difficulty Assessment (Borg Scale), and the Hospital Anxiety and Depression Scale (HADS). The EQ-5D-5L assesses five dimensions of health status—mobility, self-care, usual activities, pain/discomfort, and anxiety/depression—each rated on five levels. It also includes a visual analogue scale (VAS) ranging from 0 to 100 to evaluate the patient’s overall health status. Dyspnoea will be measured using the Revised Borg Scale (0–10 points), administered at rest and following standardized activities (e.g., sit-to-stand test), to reflect exertional breathlessness during daily tasks. The Hospital Anxiety and Depression Scale (HADS) comprises 14 items divided into two subscales—anxiety and depression—each containing seven items to evaluate corresponding symptoms. For patients unable to complete the questionnaires independently, assistance will be provided by trained research personnel to ensure accuracy and completeness. Assessments will be conducted at baseline (pre-intervention), upon completion of the 3 week intervention, and at 3 months post-intervention.

In the present study, a respiratory therapist will assess each patient’s readiness for decannulation daily and will document the decannulation attempt process and its outcome in detail. Post-decannulation follow-up will include relevant assessments within 72 h and a clinic or telephone visit during the first week. All assessments will be conducted by healthcare professionals blinded to group assignments. Ultrasound measurements will be obtained by trained physicians using a standardised protocol; respiratory parameters will be measured by qualified respiratory therapists; and quality of life will be assessed by study nurses.

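### Week-3 MIP and spirometry are specified only through an inflated tracheostomy cuff, but the protocol does not settle whether the tube is still in place at that visit

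*Protocol article*

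**What the plan says.** **Measurement condition.** For MIP, FVC, PEF and FEV1, the Protocol article (Secondary outcomes) states "The tracheostomy cuff is inflated to 25" cmH₂O, with the patient semi-recumbent. It describes no other interface. On timing: "All measurements will be performed at baseline (pre-intervention) and after 3 weeks of intervention". Table 1 agrees, with ticks at V1 and V4 (week 3).

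**Statements that allow tube removal before V4.**
- A respiratory therapist will assess each patient's "readiness for decannulation daily and will document the decannulation attempt process and its outcome in detail" (Secondary outcomes).
- Table 1 ticks readiness at weeks 1, 2 and 3, and the decannulation outcome already at V4.
- Under Primary outcome: "Successful decannulation will be defined as the absence of reintubation within 72 h following tracheostomy tube removal", and then "This outcome will be assessed at the end of the 3-week intervention".

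**Statements that suggest removal at or after V4.**
- The Primary outcome section also describes the success rate as the one that follows the three-week programme.
- Table 1 places the 72 h and one-week post-decannulation visits (V5, V6) in follow-up, after V4, and has no decannulation-outcome tick at weeks 1 or 2.
- Experimental group interventions describes a three-week programme, and the only training interface it gives is a connector to the tracheal cannula.

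**Analysis.** Statistical analysis compares continuous secondary outcomes by t-test or Mann–Whitney test, with mixed models for repeated measures. Tube status is not mentioned.

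**The concern.** Tube status at week 3 is close to being the primary outcome itself, and the trial's hypothesis is that it differs by arm. Suppose some tubes are out before V4. The plan, followed as written, then has no valid way to measure those patients. Either their week-3 values are missing, or someone improvises a different route from the one used at baseline. In both cases the patients affected are selected by the primary outcome and, if the hypothesis is right, are unequally distributed between arms. The arm difference in strength and lung function would then mix the training effect with selection or with route of measurement.

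The Introduction puts respiratory function and respiratory muscle strength first among the aims, and these measurements carry the mechanistic argument. The primary outcome and the diaphragm ultrasound do not use the cuff and are unaffected.

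**Working it through.** **Inputs**
- 30 patients per arm; planning rates as stated: "the decannulation success rate was conservatively estimated to be 50% in the control group and 80% in the TFRL-IMT group" (Sample size calculation).
- These rates rest on the pre-trial: 6/12 = 50% in controls and 10/12 = 83.3% with TFRL-IMT, the latter lowered to 80%. Those figures reproduce.
- f = share of eventual successes whose tube is out before the V4 respiratory measurement. The documents do not give f, so the full range 0 to 1 is shown, with f taken as equal in both arms and attrition ignored.

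The stated 26 per group before attrition is not used, and nothing here depends on it.

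**Step 1: what the timing statements imply.** A success needs 72 h without reintubation. If it is established by the end of week 3, the tube came out about three days before, so f = 1. If every tube stays in until the V4 measurements are done and the 72 h are counted at V5, f = 0. The text supports neither extreme outright.

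**Step 2: patients who cannot be measured as specified.** Control: 30 × 0.50 × f = 15f. TFRL-IMT: 30 × 0.80 × f = 24f. Imbalance: (0.80 − 0.50) × f, which is 30f percentage points.

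| f | No tube, control | No tube, TFRL-IMT | Cuff available, control | Cuff available, TFRL-IMT | Imbalance (points) |
|---|---|---|---|---|---|
| 0 | 0 | 0 | 30 | 30 | 0 |
| 0.25 | 3.75 | 6 | 26.25 | 24 | 7.5 |
| 0.5 | 7.5 | 12 | 22.5 | 18 | 15 |
| 1 | 15 | 24 | 15 | 6 | 30 |

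**Step 3: what a change of route could do.** If a value taken without the tube differs from a through-cuff value by s standard deviations, pooling both routes shifts the arm difference by s × 0.30 × f. The documents give no s, so these are illustrations only:
- s = 0.5: 0.5 × 0.30 × 1 = 0.15 SD at f = 1, and 0.075 SD at f = 0.5.
- s = 1: 0.30 SD at f = 1, and 0.15 SD at f = 0.5.

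**Step 4: what leaving them unmeasured could do.** At f = 1 the comparison would rest on 15 controls and 6 TFRL-IMT patients, all without a successful decannulation. At smaller f it rests on a mixture, with the patients decannulated early left out.

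**The case against.** The strongest reply is that early removal is inferred. Assessing readiness every day is not the same as removing the tube on the day readiness is met. Table 1 puts the post-decannulation visits after V4, and training as written needs the cannula for all three weeks. On that reading f is at or near 0 and the cuffed measurement is feasible. This stands as far as it goes: the timing is open. It does not dispose of the point, because the Primary outcome section also fixes the assessment of a 72 h criterion at the end of week 3, and nothing says that tubes stay in until V4. Removal of some tubes before V4 is the more natural reading, but not the only one.

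A reader might infer more than the text supports in three ways:
- *That only 6 TFRL-IMT and 15 control patients will be measurable, so that failures are compared with failures.* That is the f = 1 upper bound, not an expectation.
- *That models assuming data missing at random cannot help at all.* Decannulation status is recorded, so missingness that depends on it is not automatically non-ignorable. The difficulty is serious near f = 1, where no successfully decannulated patient has a week-3 value and any model must extrapolate from those who kept the tube.
- *That practice on the test biases MIP by a known amount.* "During the study period, MIP will be measured weekly" is described only for the TFRL-IMT arm, which also trains twice daily on the device used for outcome testing. A familiarity difference is therefore plausible. The reproducibility rule for MIP (three trials within 10%) limits it without removing it, and some of it is inherent in comparing training with no training. It is a secondary, unquantified caveat.

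It can also be said that a journal article condenses the full protocol, which may cover patients without a tube. That is fair for the missing procedure. It does not explain why the timing statements that the article does print point in different directions.

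**Conclusion.** The point holds as a need to reconcile the text, together with a cheap improvement. It is not a demonstrated bias of known size. The week-3 respiratory outcomes are tied to a cuff that some patients may no longer have. The number affected is 15f in controls and 24f in the TFRL-IMT arm, from none to an upper bound of 15 and 24. This rests on the planning rates, 30 per arm, and an f that is equal between arms and not given in the documents. If f is above 0 and the planning rates hold, the handling of these patients differs by arm, and the planned comparisons take no account of it. The size of any route effect is unknown. Only secondary outcomes are touched, in a trial that its Discussion calls exploratory.

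**What to change.** 1. Reconcile Table 1, Primary outcome, Secondary outcomes and Experimental group interventions, so that the text states whether tubes can be out before the week-3 respiratory measurement.
2. Without altering when tubes are removed, define the post-intervention MIP and spirometry as taken through the cuffed tube at week 3 or immediately before tube removal, whichever comes first, in both arms.
3. Record the day of measurement, adjust the arm comparison for the baseline value, and report any values taken after removal separately, without pooling.
4. When interpreting MIP, acknowledge that weekly testing and daily device use are described only for the TFRL-IMT arm.

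**Cost.** One existing measurement moves for some patients, and none is added. The real downside is that patients decannulated early are measured after a shorter exposure. At the planning rates this happens more often in the TFRL-IMT arm. It would tend to understate the training effect, so measurement time itself becomes related to arm. The report should say so and show the measurement day by arm.

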### Data management

The data collection process for this study will be as follows: First, the study data will be recorded in the Electronic Medical Record (EMR) system, and trained researchers will transcribe the eligible data from the EMR into the standardized electronic Case Report Form (eCRF) based on the inclusion criteria. A complete audit trail will be maintained for all data entry and modification operations to comply with the requirements of International Council for Harmonisation—Good Clinical Practice (ICH-GCP).

This study employs a three-tiered data quality control strategy: first, source data validation by comparing the consistency between entries in the EMR and the eCRF; second, real-time validation built into the system, which employs logic checking and range validation tools to promptly identify data inconsistencies; and third, cyclical quality assessment involving weekly data quality reports to monitor data status. A full-time data manager and statistician supervised data collection to ensure strict adherence to the study protocol and regulatory standards. Upon completion of patient follow-up, original data will be digitised and archived, and the eCRF retained until data lock.

In addition, An independent Data Safety Monitoring Board (DSMB) will be established, consisting of neurologists, respiratory therapists, and statisticians. The DSMB will perform biannual blinded reviews to assess data integrity, quality, and potential safety concerns, and will independently provide recommendations to the study leaders based on these findings, thereby ensuring the safety and scientific validity of the study.

### Statistical analysis

The effect of the intervention will be evaluated based on both intention-to-treat (ITT) and per-protocol (PP) principles. Between-group comparisons for the primary outcome (decannulation success rate) will be conducted using the chi-square test or Fisher’s exact test, along with calculation of relative risk (RR), absolute risk reduction (ARR), and number needed to treat (NNT). Multivariate logistic regression analysis will be used to adjust for prespecified covariates such as age, sex, and stroke type. Between-group comparisons for continuous secondary outcomes will be conducted using t-tests or Mann–Whitney U tests. Repeated measures data will be analyzed using mixed linear models. Categorical secondary outcomes will be analyzed using the same approach as for the primary outcome. Time-to-event outcomes will be analyzed using Kaplan–Meier survival analysis and Cox proportional hazards regression models.

Missing data will primarily be handled using mixed-effects models under the missing at random (MAR) assumption, with multiple imputation and complete case analysis conducted as sensitivity analyses. Prespecified subgroup analyses will include factors such as stroke type and age, with effect heterogeneity evaluated using interaction terms and controlled for multiple comparisons via the Benjamini-Hochberg method. Sensitivity analyses will also include comparisons between ITT and PP outcomes, comparisons of different statistical methods, and assessment of covariate selection strategies.

All analyses will be performed using R software (version 4.2.0), employing two-sided tests with a significance level of 0.05. The analysis will be conducted by an independent statistician, and the analysis plan was pre-specified before enrollment of the first patient to ensure reproducibility and transparency. Categorical variables will be presented as frequencies (percentages), and group comparisons will be conducted using the chi-square test or Fisher’s exact test. Continuous variables will be presented as mean ± standard deviation or median (interquartile range), depending on distributional characteristics. Group comparisons will be conducted using the t-test or Mann–Whitney U test. Safety analyses will include the incidence of adverse events and between-group comparisons.

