**Methods and analysis:**

This investigation will employ a single-center, assessor-blinded, parallel-group randomized controlled trial design, enrolling 60 post-stroke tracheostomy patients (planned age range 18–70 years; and gender distribution will be collected and analyzed). Stratified compartmental group randomization will be utilized to allocate participants to either the experimental (*n* = 30) or control group (*n* = 30) in a 1:1 ratio. Both groups will receive conventional treatment, while the experimental group will additionally undergo TFRL-IMT using an electronic device that provides inspiratory resistance which dynamically decreases with increasing lung volume for a duration of three weeks. The primary outcome measure will be the rate of successful decannulation, with secondary outcomes encompassing diaphragm function, respiratory parameters, clinical outcomes, and quality of life assessments. The primary outcome (decannulation success rate) will be compared between groups using the Chi-square test.

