## Introduction

Stroke is one of the leading cause of disability and mortality worldwide. According to the Global Burden of Disease Study (GBD) 2021 data, there are approximately 11.9 million new cases of stroke globally each year, with a total prevalence reaching up to 93.8 million (1). In the clinical management of acute stroke, about 10% of patients require endotracheal intubation and mechanical ventilation support (2). As treatment advances, 15–35% of these patients necessitate a tracheotomy to sustain long-term ventilatory support due to delayed recovery of respiratory function (3). Even after successful weaning from mechanical ventilation, 26.5% of patients still require retention of the tracheal tube (4), and only 59% of stroke patients who undergo tracheotomy are successfully extubated within 12 months (5).

Post-stroke tracheostomy patients present significant challenges in their clinical management (6). These patients frequently manifest varying degrees of respiratory dysfunction, including reduced respiratory muscle strength (7), abnormal breathing patterns (8), impaired airway defense mechanisms (9), and diminished vital capacity (10). Although tracheotomy can effectively maintain airway patency, it also prolongs the patients’ hospital stay, escalates healthcare expenditures, and elevates mortality risk and complication rates, with common complications including pneumonia, airway stenosis, and ventilation-associated lung injury (11). From a pathophysiological perspective, prolonged tracheotomy status induces respiratory muscle dysfunction (8), which subsequently results in attenuated cough reflex and compromised airway clearance, and these factors interact with each other to form a vicious circle that impedes successful decannulation (9, 12). A systematic review demonstrated that successful decannulation in post-stroke tracheostomy patients was closely related to the recovery of respiratory muscle function, suggesting that improving respiratory muscle function may be one of the key factors to facilitate decannulation (13).

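### The primary decannulation test makes no use of baseline MIP; if MIP is at least moderately prognostic, this may forgo roughly 3 to 11 points of power at 30 per arm

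*Protocol article*

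**What the plan says.** **Primary test.** The Abstract of the protocol article states: "The primary outcome (decannulation success rate) will be compared between groups using the Chi-square test". The Statistical analysis section allows chi-square or Fisher's exact test and adds relative risk, absolute risk reduction and number needed to treat. Neither place adjusts the primary comparison.

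**Supporting model.** The same section continues: "Multivariate logistic regression analysis will be used to adjust for prespecified covariates such as age, sex, and stroke type". It also lists, among the sensitivity analyses, an assessment of how covariates are selected.

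**Baseline MIP.** Table 1 schedules the respiratory parameters, MIP among them, at V1, within 24 h before the intervention. Under Secondary outcomes the article says of these parameters: "All measurements will be performed at baseline (pre-intervention) and after 3 weeks of intervention". Randomisation is stratified by age and stroke type, not by MIP.

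**Reason to expect prognostic value.** The Introduction cites a systematic review that "successful decannulation in post-stroke tracheostomy patients was closely related to the recovery of respiratory muscle function". It also describes respiratory muscle dysfunction as weakening cough and airway clearance in a cycle that hinders decannulation.

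**The concern.** A primary comparison of 30 against 30 patients on one binary outcome has little information to spare. Where a baseline measurement predicts the outcome, an unadjusted test leaves the variation it explains in the error term and does not correct for chance differences between arms. Here the measurement is already scheduled and has a plausible link to the outcome: adequate cough flow and secretion clearance are decannulation criteria, and the article connects both to respiratory muscle function.

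At stake are some power and the credibility of the result. If one arm happens to start with stronger patients, a positive or a null finding can be attributed to that, and an adjustment added after unblinding would be open to dispute.

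**Working it through.** **Inputs from the documents.** "Assuming an decannulation success rate of 50% in the control group and 80% in the TFRL-IMT group" (Sample size calculation); "employing two-sided tests with a significance level of 0.05" (Statistical analysis); 30 per arm, or 26 evaluable per arm after 15% attrition.

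**Input not in the documents.** The strength of the association between baseline MIP and success. A range is used: within-arm correlation rho from 0 to about 0.5, or AUC from 0.50 to 0.82.

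**1. The plan's own figure.** The article states that "the required sample size for each group was calculated to be 26". The pooled two-proportion formula gives

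n = [1.96·√(2·0.65·0.35) + 0.842·√(0.25 + 0.16)]² / 0.30² = (1.322 + 0.539)² / 0.09 = 38.5, so 39 per group.

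The stated 26 is not reproduced; two-sided variants give 36 (unpooled), 38 (arcsine) and 45 (continuity-corrected). This is a separate matter, but it sets the starting point here.

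**2. Power of the unadjusted test.** Power = Φ[(0.30·√n − 1.322) / 0.640].
- n = 30: Φ(0.50) = 69%. Exact calculation: chi-square 69%, Fisher 60%.
- n = 26: Φ(0.32) = 63%. Exact calculation: chi-square 65%, Fisher 54%.

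**3. Power with baseline MIP added, 30 per arm.** Outcomes were simulated from a logistic model with a standard normal covariate, calibrated to marginal success of 50% and 80%. MIP was the only covariate in the models tabulated.

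Risk-difference model with HC3 robust SE (6,000 trials per setting):

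| rho | Chi-square | Adjusted, robust SE | Logistic likelihood-ratio |
|---|---|---|---|
| 0 | 69% | 68% | 70% |
| 0.31 | 69% | 71% | 74% |
| 0.40 | 69% | 73% | 77% |
| 0.51 | 70% | 79% | 83% |

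Linear-probability model with ordinary SE (10,000 trials per setting; chi-square about 69% throughout):

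| AUC (R²) | Adjusted | Logistic likelihood-ratio |
|---|---|---|
| 0.50 (0) | 70% | 71% |
| 0.61 (0.04) | 70% | 72% |
| 0.70 (0.12) | 74% | 76% |
| 0.77 (0.22) | 78% | 80% |
| 0.82 (0.30) | 82% | 85% |

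For a moderate to strong predictor, the gain is 2 to 9 points with HC3 and 5 to 13 with ordinary SE. A further robust-SE simulation gives about 73% to 81% against 69% to 70%, hence roughly 3 to 11 points as the working range. At AUC 0.61 the gain is about 1 point or less.

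**4. With 26 evaluable per arm.** Chi-square power is about 65%. The linear-probability model gives 63%, 64%, 68%, 72% and 77% at the five AUC values. If MIP is unrelated to success, the loss is about 2 points with ordinary SE and about 4 with robust SE (the rounded figures of one run, 66% and 61%, are 5 apart). It reaches about 7 if age and stroke type are also carried and are also uninformative.

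**5. Type I error, 30 per arm.** Chi-square 5.1% to 5.7%; robust SE 4.7% to 4.8%; logistic likelihood-ratio test about 5% to 6.5%. Part of the likelihood-ratio test's apparent advantage may therefore be inflated size.

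**6. Chance imbalance.** The SE of the difference in baseline means is √(2/30) = 0.258 SD, so P(|difference| > 0.3 SD) = P(|Z| > 1.16), about 0.25. With an outcome SD of √[(0.25 + 0.16)/2] = 0.45, a 0.3 SD imbalance shifts the risk difference by rho × 0.45 × 0.3: about 4 points at rho 0.3 and 7 points at rho 0.5. The SE of the risk difference is √(0.41/30), about 12 points.

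**7. Model size.** Expected failures are 30 × 0.5 + 30 × 0.2 = 21.

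**The case against.** An unadjusted primary test with a supporting adjusted model is valid and defensible. Randomisation protects it, and a 0.3 SD imbalance in one trial in four is ordinary chance. This stands: the point concerns efficiency and robustness of interpretation, not bias.

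Four stronger readings are tempting and are not supported.

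- *MIP is left out of the adjusted logistic model.* The article introduces age, sex and stroke type as examples, says that an analysis plan was prespecified, and plans a sensitivity analysis on covariate selection. That plan is not shown. Only the absence of MIP from the primary test is established.
- *By the plan's own reasoning, baseline MIP is among the strongest predictors.* The cited review concerns recovery of muscle function, and the hypothesis concerns improvement under training. The passage on dysfunction, cough and clearance does bear on a patient's existing level, but it gives no figure. MIP is also not one of the decannulation criteria. Prognostic value is plausible, not shown.
- *Power is certainly lost and can be recovered at no cost.* The gain depends wholly on an unknown association, and adjustment costs power if that association is absent.
- *Adjustment makes up for the sample size.* With 26 evaluable per arm the linear-probability test stays below 80% even at AUC 0.82, and the likelihood-ratio test only just reaches it there.

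**Conclusion.** The point holds in conditional form. The stated primary test is unadjusted although a plausible prognostic measurement is scheduled in both arms before treatment. Under the plan's rates and 30 analysed per arm, it may forgo roughly 3 to 11 points of power if baseline MIP is at least moderately prognostic, and about nothing if MIP is weakly prognostic. It also leaves chance imbalance in MIP uncorrected, worth some 4 to 7 points on the risk difference for a 0.3 SD imbalance at rho 0.3 to 0.5. These sizes rest on an assumed association and on a logistic outcome model with a normally distributed covariate. The change is worth making because it is cheap, but it is secondary to the discrepancy between 26 and 39 per group.

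**What to change.** Before unblinding, amend the Statistical analysis section and the Abstract to name one primary analysis of decannulation success:

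- a logistic model with treatment, baseline MIP (V1, continuous) and a small, closed list of other covariates, reported as a standardised risk difference and risk ratio with robust SE;
- inference from that robust SE, not from a likelihood-ratio test. The standardised estimates match the risk-based measures already planned, which a conditional odds ratio would not;
- the chi-square test kept as the supporting unadjusted result.

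The stratification factors, age and stroke type, are the natural candidates beside MIP. Sex, for which the article gives no prognostic reason, can stay in the supporting model. With about 21 failures expected, the list should go no further. Only the V1 value should be used, because the weekly MIP readings in the experimental group come after treatment has started.

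**Cost.** A few sentences of wording, with no new visits or data. If MIP is unrelated to success, about 0 to 4 points of power are lost, rising to about 7 with 26 evaluable per arm if the other covariates are uninformative too. The tabulated gains are for MIP alone, so the sponsor should simulate the exact model chosen, including its type I error, before fixing it.
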